#### Secondary outcomes

*Anxiety* will be measured via the 7-item Generalised Anxiety Disorder questionnaire; GAD7 [46], which provides a dimensional score of anxiety symptoms which are frequently comorbid with depression. *Quality-of-life/disability* will be measured via the Work and Social Adjustment Scale; WSAS [47], which is a 5-item assessment of perceived social and work-related functional impairment used widely across a range of mental and physical disorders. *Illness perceptions* will be assessed using the Brief Illness Perceptions Questionnaire; BIPQ [48]. The BIPQ provides an insight into the participant’s views about their underlying condition – including a measure of how well they see themselves coping with its symptoms and treatments. *Alcohol use* will be measured using the self-reported Alcohol Use Disorders Identification Test (AUDIT), which has been found to be a reliable and valid method of identifying at-risk and alcohol-dependent drinkers [49]. *MDD remission*, the confirmation of continued remission status, or new remission status in participants who had previously relapsed, will be established using the IDS-SR followed by CIDI-SF. Participants scoring < 14 on the IDS-SR and who do not meet CIDI-SF criteria for MDD will be considered in a state of remission.

#### Other measurements

We will also seek to identify major changes in participants’ circumstances which may affect outcomes as well as use of RMT (such as the death of a relative or major illness), so every 3 months we are additionally collecting information about: treatments for depression, including changes in antidepressants, psychological therapies and any other action the individual has taken to alleviate depressive symptoms, and adherence to medication. The modified Client Service Receipt Inventory (CSRI [50]) is a well-validated and widely used measure of health economic data allowing us to model costs in future analyses. Change in life circumstances will be assessed using the List of Threatening Experiences – Questionnaire; LTE-Q [51].

#### Process evaluation

To ensure a system which meets participant and researcher needs, there will be continued monitoring of the acceptability and usability of the RADAR-CNS platform, including the app, assessment scheme and outcome collection platform. This will involve conducting qualitative interviews with a random selection of 15 participants enrolled within the first 3 months and thorough assessment of platform usability via self-reported questionnaires (the Post-Study System Usability Questionnaire (PSSUQ [52]) and the Technology Assessment Model Fast Form (TAM-FF; [53]). This process will be replicated in a further 15 randomly selected participants at the point of drop-out or at 1-year post-enrolment. At study endpoint, post-participation qualitative interviews will be conducted in a random selection of participants who participated until study end-point, and those who dropped out throughout the course of follow-up. Data obtained throughout the course of process evaluation will be used, if necessary, to make iterative developments to the platform software, to optimise usability of the system.

#### Follow-up procedure and data monitoring

Participants will be encouraged to live their lives as normal, responding to in-app notifications when required and completing outcomes assessments via REDCap every 3 months for the duration of follow-up. The research team will be able to periodically review incoming data using the RADAR-CNS management portal and may contact participants if there is a loss of data stream from a device, to determine whether there are issues relating to functionality or user-experience. These contacts will be recorded as evidence of feasibility and acceptability outcomes. In addition to the telephone call provided after the introductory training session, participants will receive a further call after 1-month to address any further concerns or questions, and brief follow-up telephone calls will then be offered every 3 months to maintain engagement with participants throughout the course of the study and to remind participants of any upcoming outcome assessments.

In the case of suspected depressive relapse, participants will also be contacted by research teams to perform clinical interview and risk assessment. In the case of a depressive relapse or for participants who express significant suicidal ideas, we will advise the participant to contact their treating physician. If the participant is not willing to do so, the study team may, if sufficiently concerned, make direct contact with the treating physician without participant consent. Note that participants will, at recruitment, be forewarned and be asked to consent to this procedure.

### Study debrief

At the end of the follow-up period, participants will receive a maximum 60 min “debrief” session, which will serve to collect end-point acceptability and usability outcomes, and include a qualitative interview investigating their experiences of participating for randomly selected participants. This will be done in person if possible, or over the phone if more convenient for the participant. Participants will also have an opportunity to view and discuss their own data.

### Adverse events and study withdrawal

It is not expected that participation in RADAR-MDD will increase the risk of relapse, nor of there being other significant risks of harm to participants. There may be several reasons for withdrawal from the study:Participant choosing to no longer participate; participants will be informed both in writing and verbally that participation is voluntary, that non-participation will not influence their medical care, and that they are free to withdraw from the study at any point without providing reasons.The research team may withdraw the participant in the event of inter-current illness, adverse event (AE), protocol violation, administrative or other reasons.The participant loses capacity for continued participation.

In the case of participant self-withdrawal, all attempts will be made to follow-up with the participant to establish cause of withdrawal, and to collect qualitative data regarding experience of participation. Depressive relapse itself will not be cause for automatic withdrawal; unless they choose to stop, participants who are identified as experiencing a relapse will continue to participate until study end-point. All data, including those from withdrawn participants (unless they request for their data to be deleted), will be included in the final analysis. If a participant withdraws from the study prematurely without providing evaluable data, a replacement participant will be sought if resources allow.

### Statistical and analysis plan

Descriptive statistics for demographics, attrition rate, and number of participants using the remote assessment measurements without loss or damage and providing adequate data for the duration of the study period will be estimated. Using classification/regression approaches, we will investigate whether any demographics and/or other numerical information obtained during baseline of the study might serve as a predictor for subjects drop out/percentage of adequate data. Using mixed-effect models with participants as random factor, we will estimate whether relationships between the amount of usable data during the weeks prior to the outcome assessment and obtained scale’s measurements exist.

Aggregated features obtained from biosensors, smartphones, cognitive tests and from ESM, as well as their changes from baseline or previous time points (delta features) will be used for statistical analysis. Aggregation will be done for the period of 2 weeks prior to participant’s evaluation with PHQ8 or longer time interval preceding 3-mothly outcome scale assessment, since relapse identification is done retrospectively. First, univariate approach, where each variable/feature will be modelled with use of mixed-effect models, with depressive relapse as fixed and participant as random effect, to find out which variables are influenced during the relapse. Demographics and other baseline characteristics will be added to the model, when necessary, with correction for multiple comparisons.

Secondly, we will construct predictive models, using aggregated data obtained prior to assessment of relapses and their changes from previous time points to predict binary (relapsed or not) or continuous (when scale score is treated as continuous variable) outcomes. Under assumption that data are missing at random, multiple imputation will be applied for covariates, where missing-ness is not drastically high. Multivariate prediction model will be constructed and variable selection, based on, for example, LASSO L1-regularization for linear models, or different feature selection algorithms will be applied. Models’ performance will be characterized through the cross-validation, putting stress on sensitivity and specificity of relapse prediction model.

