T: Telephone. F2F: face-to-face. R: REDCap web-based platform. pRMT: passive remote measurement app. aRMT: active remote measurement app. (X): clinical interview only conducted in people identified as MDD relapse cases by IDS-SR/CIDI-SF primary outcome measurement. X delivered once per month. XX delivered twice per month (every 2-weeks). *ESM and cognition tests are conducted once every 6 weeks

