#### Active RMT (aRMT) app

Following extensive focus group work and user testing [31], an additional app has been created to administer the aRMT aspects of the study protocol. This includes validated questionnaires to measure depressive symptoms and self-esteem. Variability of depressive symptoms will be measured via the 8-item Patient Health Questionnaire (PHQ8; [38]) every 2 weeks throughout the course of follow-up. Variation in self-esteem will be measured using the Rosenberg Self-Esteem Scale; RSES [39]. The RSES is a widely-used 10-item self-reported questionnaire used to quantify self-esteem along a continuum and will be administered alongside the PHQ8 every 2 weeks.

As with the PHQ8 and RSES, every 2- weeks participants will be asked to complete a speech task. This requires participants to say aloud, in a quiet area, some excerpts from “The North Wind and the Sun”, which are shown to be phonetically balanced across all three languages [40]. These will be offered on a random schedule to prevent rehearsal and fluency and preserve prosodic features. In addition to this, participants will be asked to respond to the following question: “Can you describe something you are looking forward to this week?”

The aRMT app will also deliver an ESM schedule (see online Additional file 1), which has been designed to collect brief, in-the-moment assessments relating to several of our domains of interest: mood, stress, sociability, activity and sleep. Participants will receive a series of questions intended to reflect their current state (such as “right now, I feel content”), with 7-point Likert scale answer options (0 = Not at all, 7 = Very much). The ESM schedule consists of approximately 44 items, taking up to 3-min to complete, delivered 9 random times per day within 90-min blocks starting from 08.30 and ending at 22.00 for 6 consecutive days every 6 weeks.

Cognitive function will also be measured using the THINC-IT® app, which has been specifically designed and validated to screen for cognitive dysfunction in depression [41], and includes assessments of elements of executive function such as memory, concentration, and attention.

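### The univariate relapse model has no session or time term, so practice gains on the repeated THINC-IT tests can bias the relapse coefficient if MDD-positive assessments become rarer or commoner over follow-up

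*Protocol article*

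**What the plan says.** All points are from the Protocol article.

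- **Features** (Statistical and analysis plan). The sources are "Aggregated features obtained from biosensors, smartphones, cognitive tests and from ESM". Levels are used, "as well as their changes from baseline or previous time points (delta features) will be used for statistical analysis". Either baseline or an earlier time point may therefore be the reference for a change.
- **First-step model** (same section). Each feature is modelled "with depressive relapse as fixed and participant as random effect, to find out which variables are influenced during the relapse".
- **Covariates allowed in that model** (same section). "Demographics and other baseline characteristics will be added to the model, when necessary, with correction for multiple comparisons". No session, visit or time variable is named.
- **Second-step predictive model** (same section). It is built "using aggregated data obtained prior to assessment of relapses and their changes from previous time points to predict binary" or continuous outcomes. Only previous time points are named as the reference here.
- **Test schedule** (Study procedures, Table 2 and its footnote). THINC-IT is first scheduled at month 0, and "ESM and cognition tests are conducted once every 6 weeks".
- **Practice** (Active RMT app). For the read-speech excerpts the article says: "These will be offered on a random schedule to prevent rehearsal and fluency and preserve prosodic features". It states nothing comparable for THINC-IT, which covers memory, concentration and attention.

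**The concern.** Scores on repeated tests of memory and attention may rise with familiarity. The participant random effect removes stable differences between people, but not a trend that all participants share across sessions. The covariates the model allows are fixed at baseline, so they do not remove it either.

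The relapse coefficient then compares a participant's MDD-positive assessments with the same participant's other assessments, whenever each occurred. If positive assessments fall mostly early, they coincide with low, unpractised scores, and part of the learning curve is credited to relapse. If they fall mostly late, practice offsets a real decline.

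The document makes a drift in prevalence plausible:

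- Study population admits people whether or not they are currently depressed.
- The primary outcome is presence of MDD during follow-up, with no prior remission required in the definition. People depressed at entry can therefore count as positive early.
- The Discussion expects that self-monitoring may lower relapse risk and that drop-out may itself represent relapse. Either could lower the prevalence observed later.

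What is at stake is the list of cognitive features declared to change during relapse. Wearable, phone and ESM features are not performance tests, so this mechanism does not apply to them in the same way.

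**Working it through.** The plan gives no figure for this point to reproduce. The check asks how many sessions there are, and how large the bias could be under stated assumptions.

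**1. Number of sessions.** From the 6-week interval and follow-up of up to 2 years: 104 / 6 = 17.3, so about 17 (18 if month 0 is counted as an extra session). At 1 year: 52 / 6 = 8.7. These are maxima, because follow-up is up to 2 years and there will be attrition.

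**2. Bias formula.** Take a score with a participant effect, a practice curve g(t) and no true relapse effect. At visit t (t = 0 to 8, the baseline and eight quarterly assessments) the probability of being MDD-positive is p(t), independent of the score. For T visits, the within-participant relapse coefficient, which a random-intercept model approximates closely here, tends to

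bias = Σ p(t)[g(t) − mean g] / { Σ p(t) − [Σ p(t)(1 − p(t)) + (Σ p(t))²] / T }

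If p(t) is constant the numerator is zero, so flat prevalence gives no bias.

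**3. Assumed inputs (none is in the documents).** p(t) falls in a straight line from 0.30 to 0.10. g(t) = gain × (1 − exp(−t/τ)), with τ = 3 quarters (slow) or 0.75 quarters (fast). Between-person SD is 0.8 and within-person SD 0.6, so the total SD is √(0.64 + 0.36) = 1 and results are in SD units.

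**4. Worked case: gain 0.5, slow curve, all nine visits.** g = 0, 0.142, 0.243, 0.316, 0.368, 0.406, 0.432, 0.452, 0.465, with mean 0.314. Numerator: −0.0814. Denominator: 1.80 − (1.4025 + 3.24)/9 = 1.284. Bias = −0.0814 / 1.284 = −0.063. Without the enrolment visit: −0.0461 / 1.070 = −0.043.

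**5. False deficit by gain, same formula.**

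| Curve | Rows used | Gain 0.3 | Gain 0.5 | Gain 0.8 |
|---|---|---|---|---|
| Slow | all nine visits | 0.04 | 0.06 | 0.10 |
| Slow | without enrolment | 0.03 | 0.04 | 0.07 |
| Fast | all nine visits | 0.03 | 0.05 | 0.08 |
| Fast | without enrolment | 0.01 | 0.01 | 0.02 |

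**6. False positives.** These come from simulation of 500 people with the slow curve and no true effect, as the share of runs with p < 0.05 before any multiplicity correction, for gains 0.3 / 0.5 / 0.8. With prevalence falling from 30% to 10% and all visits: 33 / 73 / 97%. Without the enrolment visit: 18 / 40 / 74%. With prevalence falling from 25% to 15% and all visits: 14 / 24 / 51%. With flat prevalence: 4 to 5%. With log of session added: 4 to 7% throughout.

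**7. Direction when there is a true effect.** A separate simulation used a true effect of −0.30, an assumed gain of 0.6 and 600 people. Positives spread evenly gave −0.30, mostly early gave −0.43, and mostly late gave −0.23. With a visit effect added, all returned to about −0.30.

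**The case against.** **The plan may already deal with it.** The article condenses the plan, and an unseen SAP could add a time term. That is possible. But the point does not rest on silence: the section writes out the fixed effect, the random effect and the kinds of covariate allowed, and that form is the vulnerable one.

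**Change scores.** A reader might infer that all change scores are taken from the first administration. The text does not support this. It allows baseline or previous time points, and the predictive model names previous time points only. In simulation, previous-time-point changes were nearly unaffected: 7 / 8 / 8% false positives at gains 0.3 / 0.5 / 0.8 with prevalence falling from 30% to 10%.

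**Baseline as reference.** A reader might also infer that a change from baseline by itself hides a decline as large as the practice gain. That would be true of a raw comparison with the first session. It is not true of the stated model: subtracting baseline takes one constant off all of a participant's later rows, so the within-participant contrast over those rows is unchanged. The distortion comes from the missing time term.

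**Speech.** Read speech, at up to 104 / 2 = 52 sessions, looks exposed in the same way. But the article states a countermeasure, adds an open question in free speech, and does not list speech separately among the feature sources. It is a secondary concern.

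**Size.** The gain, the curve and the drift are all assumptions. With a fast curve and the enrolment row excluded, the bias is 0.01 to 0.02 SD. The planned multiplicity correction would lower the false-positive rates, though not the bias. All of this stands and limits the weight of the point.

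**Conclusion.** The concern holds for the THINC-IT features in the univariate relapse model. As written, that model cannot separate practice from relapse when the frequency of MDD-positive assessments changes over follow-up. The bias can go either way. Under the assumptions shown, with prevalence falling from 30% to 10%, it is a false deficit of about 0.01 to 0.10 SD for gains of 0.3 to 0.8. It is zero if prevalence is flat and small if learning levels off quickly. The bias is modest in absolute size, but with several hundred participants it can be enough to label a cognitive feature as relapse-related when it is not. The study's aims do not stand or fall on this, since cognition is one data stream among several. It is a cheap improvement to a stated model.

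**What to change.** In the first-step models, at least for cognitive features, add session number or time since enrolment as a fixed effect, curved in its early part (for example log of session). Offer the same variable as a candidate in the predictive model. The same term can be added for read speech as a precaution.

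This is a change of analysis wording and needs no new data, provided each test is stored with its date. The cost is one or two parameters per model and a little precision where relapse and time are correlated. A log term suits a gradual curve. Visit as a category absorbs any common shape, at the price of eight parameters for nine visits, and would serve as a sensitivity check. Reporting the proportion of MDD-positive assessments at each visit would show whether the bias was a live risk.

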### Study objectives

RADAR-MDD is a clinical study aiming to assess the utility of multi-parametric RMT in clinical populations with MDD.

Specifically, RADAR-MDD aims to:Determine the usability, feasibility and acceptability of, and adherence to, RMT to provide real-time objective multidimensional indications of clinical state in individuals with MDD.Improve and refine clinical outcome measurement using RMT as a means of identifying current clinical state.Determine whether multi-parametric RMT collected in populations with recurrent MDD can provide information predictive of depressive relapse and other critical outcomes including anxiety, quality-of-life, and MDD remission.

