#### Primary outcome

##### Major depressive disorder relapse

The presence of MDD during follow-up will be defined as meeting criteria for MDD according to the Wold Health Organisation’s Composite International Diagnostic Interview – Short Form (CIDI-SF; [44]). The CIDI-SF has been used extensively on web-based platforms, and has shown excellent sensitivity and specificity to identify current MDD state [44]. Additionally, a score of > 25 on the the Inventory of Depressive Symptomatology – Self-Reported (IDS-SR; [45]) will be required to establish that the severity of the depressive episode is at least moderate. The IDS-SR is a 30-item questionnaire, widely used in depression trials and providing detailed information on depressive symptoms, including all 9 Diagnostic and Statistical Manual (DSM) domains, symptoms commonly associated with depression (such as irritability or pain), melancholic symptoms and atypical symptoms. Scores on each of the 30 items are summed to create a total score ranging from 0 to 84, with the following thresholds: 0–13 (no symptoms); 14–25 (mild symptoms); 26–38 (moderate symptoms); 39–48 (severe symptoms); 49–84 (very severe symptoms) [45]. In the case of IDS-SR/CIDI-SF identified relapse, a confirmatory diagnostic interview will be conducted, to additionally confirm of relapse onset.

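### The relapse-prediction features run up to the assessment that detects a current episode, with no lead time, so for relapsers they partly describe the episode itself

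*Protocol article*

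**What the plan says.** The section Statistical and analysis plan fixes the end of the feature window: "Aggregation will be done for the period of 2 weeks prior to participant’s evaluation with PHQ8 or longer time interval preceding 3-mothly outcome scale assessment". The second option carries its reason with it: "longer time interval preceding 3-mothly outcome scale assessment, since relapse identification is done retrospectively". Changes from baseline or from earlier time points are used as well.

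Two stages follow. The first is univariate: each feature is modelled with relapse as a fixed effect, "to find out which variables are influenced during the relapse". In the second, "we will construct predictive models, using aggregated data obtained prior to assessment of relapses and their changes from previous time points". Performance is judged by cross-validation, with emphasis on sensitivity and specificity.

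The section Major depressive disorder relapse defines the outcome as meeting CIDI-SF criteria for MDD together with an IDS-SR score above 25, and presents the CIDI-SF as a tool for identifying MDD that is present now. For participants who screen positive, "a confirmatory diagnostic interview will be conducted, to additionally confirm of relapse onset". Outcome measurements and Table 2 place these assessments every three months.

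Study objectives keeps two aims apart. Objective 2 is to identify current clinical state. Objective 3 is to learn whether remote measurement "can provide information predictive of depressive relapse and other critical outcomes".

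**The concern.** An episode found to be present at an assessment began before that assessment. A feature window that runs up to the assessment therefore takes in days on which the participant was already depressed. Nothing in the analysis section places a gap before onset or removes the days after it.

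What is at stake is the meaning of the main predictive result. Sleep, activity, sociability and speech are expected to change during a depressive episode. A model given those days can separate relapsers from non-relapsers without any signal that came before the relapse. Its accuracy would then be read as early warning, which is the use that the Abstract and Background put forward, when it may be recognition of an episode already under way. Objective 3 would be left unanswered, and the reported sensitivity and specificity would not show it.

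**Working it through.** The article gives no figure for the overlap, so there is none to reproduce. The size is derived as follows.

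**Inputs from the article**
- Window end: the outcome assessment (Statistical and analysis plan).
- Assessment interval: three months, taken as 13 weeks or 91 days (Outcome measurements, Table 2).
- Episode present at the assessment: follows from the description of the CIDI-SF (Major depressive disorder relapse).

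**Assumptions not in the article**
- Onset is uniform over the 13 weeks before the assessment, and the episode lasts until the assessment.
- The longer window is 4, 13 or 26 weeks. The article says only that it is longer than the 2 weeks used for the PHQ8.

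**Step 1: share of the window after onset.** Let *t* be the weeks from onset to assessment, uniform on 0 to 13, and *w* the window length. The post-onset share is min(*t*, *w*)/*w*. For *w* up to 13 its mean is 1 − *w*/26, and the probability that the whole window is post-onset is 1 − *w*/13. For *w* above 13 the mean is 6.5/*w*, and no window is wholly post-onset.

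| Window | Mean post-onset share | Wholly post-onset |
|---|---|---|
| 4 weeks | 1 − 4/26 = 0.846 | 1 − 4/13 = 0.692 |
| 13 weeks | 1 − 13/26 = 0.50 | 0 |
| 26 weeks | 6.5/26 = 0.25 | 0 |

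**Step 2: sensitivity to episode duration.** Suppose instead that the episode has lasted at least 14 days by the assessment, with *t* uniform on 14 to 91 days. For a 91-day window the mean share is 52.5/91 = 0.577. For a 28-day window, 63/77 = 0.818 of windows lie wholly in the episode. The other 14/77 = 0.182 have a mean share of 21/28 = 0.75. The total is 0.818 + 0.182 × 0.75 = 0.954.

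**Step 3: what this can do to apparent accuracy.** Take a feature with no signal at all before onset, whose level shifts by *d* SD on in-episode days. Its window mean is then *d* × (post-onset share) plus standard normal noise for relapsers, and standard normal noise for non-relapsers. Simulation with 400,000 draws per setting gives these AUCs:

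| *d* | 28-day window | 91-day window | Window ending at onset |
|---|---|---|---|
| 0.5 | 0.617 | 0.569 | 0.50 |
| 0.8 | 0.682 | 0.610 | 0.50 |
| 1.0 | 0.722 | 0.634 | 0.50 |

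The values of *d* are illustrative. The table shows that discrimination above chance can arise with no predictive content.

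**The case against.** The strongest defence is that the authors saw the problem. They lengthen the window because relapse is identified after the fact, and they add changes from earlier time points. Both bring in data that may precede onset. This stands in part: the contamination is partial. It does not remove the concern, because data from before and after onset are pooled in one aggregate, and a change score still has a possibly in-episode value as its current term.

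A second defence is that window lengths and lead times belong in an analysis plan that is not shown. That is fair for the length. The anchor, however, is stated in the article with a rationale, and the predictive models are tied to it.

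Some stronger readings are tempting and are not supported:
- A reader might apply the 2-week window to relapse and conclude that about 92% of the data are post-onset and that 85% of windows lie wholly inside the episode. The article ties the 2-week window to the PHQ8. Relapse is judged at the 3-monthly assessment, for which only a longer interval is stated.
- A reader might infer that both modelling stages share one window and that objectives 2 and 3 collapse into a single analysis. The article does not say that the stages use the same length, and the models differ: the feature is the outcome in the first stage and the predictor in the second.
- A reader might take it that an onset date is already on file. The wording about the confirmatory interview is unclear and does not say that a date is recorded. The interview is held only for those who screen positive. Any date would rest on recall, which the Background itself describes as possibly biased.

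**Conclusion.** The concern holds for the relapse-prediction models. The assessment anchor is stated, no lead time or exclusion of post-onset data accompanies it, and no other section of the article repairs it. The anchor is suitable for objective 2 and for the univariate stage, which asks what changes during a relapse.

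For windows of 4 to 13 weeks, between about 85% and 50% of a relapser's predictor data would fall after onset on average. A 26-week window would bring this to about 25%. These figures rest on uniform onset within the quarter and on an episode that persists to the assessment. The first is purely an assumption. The second is supported by the article's account of the CIDI-SF. If relapse were also counted for episodes that had ended before the assessment, some windows would contain post-episode data too, which would not help.

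Accuracy obtained this way cannot by itself establish prediction. It does not follow that there is no pre-onset signal, only that this analysis could not tell the two apart. No data are lost, since sensor collection is continuous and the windows can be cut again at analysis.

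**What to change.** 1. For objective 3, make the main analysis a lagged one: predict relapse at each assessment from features collected up to the preceding assessment, among participants not in MDD at that preceding assessment. For them the detected episode began later, so the features precede it. The at-risk set must be written down, because Study population admits people whether or not they currently have symptoms.
2. Where the confirmatory interview yields a usable onset date, add an analysis whose windows end a prespecified lead time before onset. Give non-relapse intervals index dates with a comparable distribution within the quarter.
3. Keep the assessment-anchored models and report them as detection of current state, under objective 2.
4. State the length of the longer window.

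The cost is analysis-plan wording and re-extraction of features. The lagged analysis needs no new data from participants. It loses intervals that begin in an episode or lack a preceding assessment. At the article's own rate, 600 × 0.33 = 198 relapses would be expected in one year before attrition, against the 100 it requires. There is nominal room, but the article does not allow the loss to be estimated. Features up to three months old may miss late warning signs, so reported accuracy will probably be lower.
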